#### 10.2.2.4 Adverse Events not Requiring Expedited Reporting

The occurrence of any of the following adverse events does not require expedited reporting unless unusually severe and/or causing prolonged hospitalization:

Hypotension, fatigue (lethargy, malaise, asthenia), fever, rash/desquamation, nausea, vomiting, SGOT (AST) serum glutamic oxaloacetic transaminase),

SGPT (ALT) (serum glutamic pyruvic transaminase), acidosis, hyperglycemia, hypocalcemia, syncope (fainting), headache, myalgia (muscle pain), apnea, and hypoxia.

#### **10.2.2.5 Institutional Review Board (IRB) Reporting**

The reporting of adverse reactions described in the tables above is in addition to and does not supplant the reporting of adverse events as part of the report of the results of the clinical trial, e.g. study summary forms or coeprative group data reporting forms.

### **Baseline Medical Condition**

Uncontrolled intercurrent illness including, but not limited to, ongoing or active infection, symptomatic congestive heart failure, unstable angina pectoris, cardiac arrhythmia, or psychiatric illness/social situations that would limit compliance with study requirements is an exclusion criterion. Due to the minimal toxicity of the agents under study, all other patients are eligible, with ECOG status  $\leq 2$ .

### **Laboratory Tests/Other Evaluations**

Serum PSA, testosterone, Estradiol, lycopene and omega-3/6 ratio will be determined. Details of other molecular tests are given in the study design sections.

### **Vital Signs**

Vital signs will be obtained at each patient visit. Abnormal vital signs will be reported as defined in the common toxicity criteria above.

## **10.3 Adverse event reporting**

See section 10.2

## **10.4 Consent**

Verbal and written consent for participation will be obtained by the patient's physician. Additionally, patients will be asked to provide consent for each tissue donation, even if they have already agreed to participate in a previous tissue donation for the project.

## **10.5 Confidentiality, risks, and protection of subjects**

### **Risks/discomforts**

Conservative management of early prostate cancer has been reported as a successful option for select patients. However, it remains an experimental approach, and it is possible that patients may experience disease progression in excess of that which would have occurred with primary active treatment. Furthermore, patients may experience adverse psychological impact by deferring active treatment for known cancer. Patients wishing to end participation in the study for this reason may do so at any time and proceed with active treatment. Additional prostate biopsy entails slight discomfort and minimal additive risk of bleeding and/or infection. Anesthetic risk is minimized by the use of local nerve block.

### **Compensation for injury**

Any injury resulting from prostate biopsies for the purposes of this study will be compensated per the standard policies of the University of California and/or the Veterans Administration, as appropriate.

### **Alternatives**

Patients are free to decline participation with no impact whatsoever on their patient status at UCSF or its affiliates; they may also withdraw from the study at any time. Patients declining or withdrawing will be offered standard definitive treatment for prostate cancer as appropriate by their physician.

### **Costs and reimbursement**

The National Cancer Institute will supply the lycopene, fish oil and placebo supplements. The cost of office visits, laboratory tests and biopsies, (except for the three month research biopsy) will be billed to patients and/or insurance companies in standard fashion. Every effort will be made to obtain authorization from patients' insurance companies for all treatments, tests, and doctors office appointments. Insurance companies have sometimes refused to pay for the costs of standard treatment for patients on research studies, in which case patients will be responsible for

all costs. Patients should check with the doctors and/or financial counselor if they have questions regarding the costs of treatment and your eligibility for payment programs.

There will be no reimbursement to subjects for participation.

### **Confidentiality**

Specimens will be assigned accession numbers that are unique for the project, and no reference is made to any patient identifier. In order to determine clinical endpoints, we must review patient's records. Every precaution will be taken to preserve patient confidentiality – access to patient identifiers is limited to the database manager, and principal investigators. The identifier will be recorded in a logbook in addition to the signed consent forms and stored in a locked cabinet in the principal investigator's office. No laboratory results will be reported back to the patient or his physician, and no patient contact is made unless specifically requested by the patient. No individual patient will be identified in any publication.

## **10.6 Ethics**

For men who elect watchful waiting, there is no generally accepted standard of care. This study will assess whether nutrition supplements lead to desirable molecular changes. The use of a placebo controlled trial is ethical in this circumstance, since there is no data to support that denying active intervention with either lycopene or fish oil would lead to harmful cancer progression.

## **10.7 Compliance with laws and regulations**

This protocol will be subjected to institutional review board scrutiny. Regulations for consent and adverse event reporting will be followed.

## 11 Ancillary Therapy

### 11.1 What is allowed during treatment

No other treatments for prostate cancer (surgery, radiation, hormonal therapy, chemotherapy, investigational agents, or herbal preparations) will be allowed during the three months of the primary study period. Patients will be asked to refrain from taking additional dietary supplements beyond those provided by protocol.

## 12 Removal of Patients from Protocol Therapy

Patients will be removed from protocol therapy for clinical progression defined above. They will then be offered standard active therapy for their prostate cancer.

## 13 Statistical Considerations

Patients satisfying eligibility requirements will complete a dietary questionnaire prior to randomization.

Patients will not be taking lycopene or omega-3 supplements, but other dietary sources of tomato lycopene or fish oil could possibly influence the assessment of outcome for this study. For example, it might be that an excess of tomato-consuming patients would be placed in the control arm, confounding the assessment of gene expression in response to lycopene. Therefore, patients will be stratified into four groups (low tomato/low fish, low tomato/high fish, high tomato/low fish, and high tomato/high fish) and block-randomized to placebo, lycopene, or fish oil, within these strata. This will avoid the chance occurrence of confounding due to usual intake of fish or tomato products (e.g. unbalanced patient features among the study arms). Cutoffs for the baseline dietary strata are based on the medians of intake from a **completed** independent pilot study on 96 prostate cancer patients from the source population at the UCSF Mt. Zion Cancer Center, who completed the Willett Semi-Quantitative Food Frequency Questionnaire. The median for total tomato consumption was 4 servings/week; for fish consumption it was two servings/week.

We will assess changes in serum lycopene and omega-3 fatty acid pre- and post-intervention to assess compliance and the physiologic significance of the supplementation doses.

For our primary analysis, changes in gene expression for each of the two nutrient interventions will be compared with that of the control arm. The two intervention arms will not be compared with each other. The primary outcome measure will be at least a two fold up decrease in gene expression of *IGF-1* or *COX-2* at three-months relative to the initial biopsy for a given patient (both normalized to levels of a control housekeeping gene,  *$\beta$ -glucuronidase*). To compare the intervention and control groups, we define an important difference to be a 40% difference in the proportion of patients on the intervention arm compared with the placebo arm who satisfy the primary outcome measure defined above (e.g. 20% in control vs. 60% in intervention showing at least a two-fold decrease in mRNA level). Fisher's exact test for proportions will be used to determine if *IGF-1* or *COX-2* mRNA levels are statistically significantly different between the groups.

For the secondary specific aims (aims 1.2 through 1.4 defined above), we will consider a microarray dataset with measurements for 30,000 genes. For this exploratory investigation genes will be treated as being independent so as to first identify all possible genes that may indicate an effect due to the nutritional supplement (Aim 1.2) or to other dietary components (each considered as a binomial variable) (Aim 1.3). Fisher's exact test will be used to determine which genes result in differences in proportions with up or down regulated genes between groups. No adjustment for multiple comparisons will be made. Also, after all patients have had the potential to be followed for at least one year, they will be classified as to whether they had experienced disease progression within 1 year from protocol entry. The same exploratory techniques described above first using the baseline gene expression profile will be carried out to identify genes that may be associated with disease progression (Aim 1.4). Even though any nutritional supplement will be stopped at 3 months from the start of protocol therapy and the duration of any effect is unknown, this analysis will be repeated using the 3-month gene expression profile to identify the effects of any gene that might have been modified by protocol treatment. To account for genes with highly variable expression regardless of study arm, genes whose expression levels change two-fold in more than 20% of men on placebo (comparing three-month to baseline) will

be excluded from subsequent consideration. This might exclude possible predictors of outcome, but if there is variability within the placebo group then the results may be biased. This refining process will isolate potential predictors of nutritional change when assessing the primary as well as the secondary outcomes. Standard microarray gene expression software algorithms will facilitate analyses to determine if there are individual genes or clusters of genes associated with either supplement, dietary component or disease progression[62, 63] . Fisher's exact test will be used to determine which genes result in statistically significant differences between the groups.

To evaluate the primary study aim, 29 patients will be randomized to the lycopene intervention, 29 to the fish oil intervention and 29 to the control arm. Analysis of 87 evaluable patients is sufficient to detect a 40% difference in the proportion of patients with a 2-fold decrease in *IGF-1* mRNA levels with lycopene or in the *Cox-2* gene with fish oil when compared with the control. The total accrual of 97 patients takes into consideration a 10% dropout rate by the time of the three-month biopsy. The level of significance for a directional test is set at .025 because the control group will be compared with each of the two intervention groups. The power of each test is set at 81% (nQuery).

Descriptive statistics (mean, confidence intervals, median, proportions) will be calculated to characterize the patients' baseline disease features (e.g. age, Gleason score, PSA) and self-reported nutritional dietary data within each arm. Differences between each of the intervention arms and the placebo arm will be assessed using a chi-square statistic for categorical variables, a t-statistic for continuous variables and the Mann-Whitney statistic for distributions. Estimates of the probability of remaining free of disease progression will be calculated using the Kaplan-Meier product limit method. The log rank test will be used to compare tumor progression between each supplement group and the control (Aim 1.5).

The randomized clinical trial design of this study limits the potential for confounding due to other factors, however this will be investigated by comparing the distribution of clinical parameters and other diet/lifestyle factors as well as changes after 3 months of study treatment among the three arms. Unequally distributed factors would only bias the results if they also

correlate with changes in gene expression. If necessary, the Mantel-Haenszel test for a stratified analysis would be performed in evaluating the primary study aim.

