## 1. Objectives

- 1.1 Primary: To measure gene expression in normal prostate tissue acquired by needle biopsy in men assigned to placebo, lycopene or fish oil nutritional supplements at baseline and after intervention. The primary outcome measure is a two-fold decrease in mRNA transcript level. The primary study endpoint is the difference in the proportion of the patients in a nutritional supplement arm compared to a placebo control arm achieving a two-fold decrease in the gene of interest. Quantitative polymerase chain reaction will assess modulation of expression of the *insulin-like growth factor 1 (IGF1)* and the cyclooxygenase 2 (*Cox-2*) gene in lycopene and fish oil recipients respectively.
- 1.2 Secondary: We will use cDNA microarrays with 30,000 independent clones to identify new candidate molecular targets for lycopene and omega-3 response pathways deserving further study.
- 1.3 Secondary: To correlate baseline gene expression patterns determined by cDNA array analysis with self-reported dietary intake. Based on previous epidemiologic, *in vitro*, and *in vivo* studies, we hypothesize that higher intake of total energy, fat/meat/animal products, dairy/calcium, and lower intakes of fish, vegetables, tomatoes/lycopene, vitamin E, and selenium will be associated with particular gene expression profiles.
- 1.4 Secondary: We will assess if there are gene expression patterns correlated with progression or lack of progression as assessed at a time point 12 months after study entry.
- 1.5 Secondary: We will assess if lycopene or omega-3 supplements affect the incidence of tumor progression.

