#### **3.2 Outcome measures**

##### **3.2.1 Primary outcome measures**

The twofold decrease in mRNA transcript level detected by Taqman quantitative polymerase chain reaction comparing baseline to three-month normal prostate biopsies will be the primary outcome measure. Histologic examination of the needle biopsy tissue will be used to verify that RNA is prepared only from normal prostate areas. (Where possible, areas of tumor histology will be assessed in parallel, though assays based on these tissues will not form part of the primary outcome measure). We will specifically assess the effect of lycopene supplementation on *IGF-1* and the effect of fish oil supplementation on *Cox-2* when compared to the placebo control group.

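### The two-fold yes/no primary endpoint with Fisher's exact test is correctly sized but inefficient: it ignores the size of the PCR change, the baseline level and the diet strata

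*Protocol*

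**What the plan says.** All references are to the Protocol.

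- **Endpoint.** Section 1.1 compares responder proportions, a response being a halving of the target gene's mRNA: "The primary study endpoint is the difference in the proportion of the patients in a nutritional supplement arm compared to a placebo control arm achieving".
- **Measurement.** Section 3.2.1 names what lies beneath it: "The twofold decrease in mRNA transcript level detected by Taqman quantitative polymerase chain reaction comparing baseline to three-month normal prostate biopsies". Section 13 adds that both values are normalised to a housekeeping gene. Every man with both biopsies therefore has a quantitative change.
- **Effect size.** Section 13 declares: "we define an important difference to be a 40% difference in the proportion of patients on the intervention arm compared with the placebo arm", with the example "20% in control vs. 60% in intervention showing at least a two-fold decrease in mRNA level".
- **Test.** Section 13 names the method for deciding whether expression of the two genes differs between arms: "Fisher's exact test for proportions will be used to determine if".
- **Level and size.** Section 13 splits the level over the two comparisons: "The level of significance for a directional test is set at .025 because the control group will be compared with each of the two intervention". Stated power is 81% per test with 29 evaluable men per arm, and 97 are accrued to allow for 10% dropout.

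No analysis of the PCR change as a quantity is stated, and no reason is given for the two-fold cut. The t and Mann-Whitney statistics in Section 13 follow the sentence on baseline disease features and dietary data. The Mantel-Haenszel fallback would still use the yes/no outcome.

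**The concern.** Cutting a measured change at one threshold throws away how far each man lies from it. A 1.9-fold and a 2.1-fold fall count as opposite results, while a 2.1-fold and a 5-fold fall count as the same. Three further features add to the loss:

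- Fisher's test is conservative at this sample size.
- The baseline expression level, which is related to any change from baseline, is not used.
- The four tomato/fish strata, created to protect this very comparison, do not enter the planned test.

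Section 13 also describes the test as deciding whether mRNA levels differ, but a comparison of responder proportions addresses that only indirectly.

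What is at stake is power. The three-month research biopsy is outside standard practice and paid for by the study (Section 8.3), so information lost from it is costly.

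**Working it through.** **1. Inputs (Section 13).** Control 20%, intervention 60%, 29 per arm, one-sided α = .025, Fisher's exact test, stated power 81%.

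**2. Reproduce the plan.** Summing the two binomial probabilities over all tables with one-sided Fisher p ≤ .025 gives power of 80.2% at 27 per arm, 82.3% at 28 and 83.0% at 29. So 28 per arm already reaches 81%, and the stated 29 is slightly conservative. Accrual: 87 / 0.90 = 96.7, rounded up to 97. Both figures hold.

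**3. True size of the test.** The same sum with 20% in both arms gives 0.0106, against the nominal .025.

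**4. Translate the planned effect to the measured scale.** The Protocol gives no SD or distribution. *Assume* log2 fold change is normal with equal SD in both arms. Then 20% vs 60% beyond the same cut is a shift of z(0.60) − z(0.20) = 0.253 + 0.842 = 1.095 SD.

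**5. Compare power** at 29 per arm and one-sided .025. The t-test power comes from the noncentral t with 56 df and noncentrality d·√(29/2).

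| Responders | Shift (SD) | Fisher | t-test on log2 fold change |
|---|---|---|---|
| 20% vs 60% | 1.095 | 83% | 98% |
| 20% vs 50% | 0.842 | 57% | 88% |
| 20% vs 40% | 0.588 | 28% | 60% |

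For 81% power at the planned effect the t-test needs 15 per arm and Fisher 28. With 29 per arm the t-test has 81% power at a 0.76 SD shift (20% vs about 47%), where Fisher has about 47%.

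**6. Drop normality.** Simulations with responders held at 20% and about 60%, 29 per arm, one-sided .025:

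| Distribution of log2 change | Fisher | t-test | Mann-Whitney |
|---|---|---|---|
| Normal | 83% | 98-99% | 98% |
| Heavy tails, t with 3 df | 82-84% | 81-83% | 94% |
| Heavier tails, t with 2 df | 82-83% | 62% | about 92% |
| Half the men shift strongly, half not at all | 83% | 98% | 91% |
| 60% of men shift, 40% not at all | 83% | 95% | 94% |

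Ranges are between repeated runs. The t-test's advantage depends on the distribution. The rank test beat Fisher in every case tried.

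**7. What baseline adds (normal case).** With equal variances and baseline/3-month correlation ρ, adjusting for baseline multiplies the error variance of the change by (1 + ρ)/2. *Assume* ρ between 0.3 and 0.6, since the Protocol gives none. For a 0.75 SD shift (20% vs about 46%), where the plain t-test has 80%:

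- ρ = 0.6: 0.75/√0.80 = 0.84 SD, power 88%
- ρ = 0.3: 0.75/√0.65 = 0.93 SD, power about 93-94%

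**8. The two-comparison split.** Exact Fisher power is .830 at .025 and .896 at .05. Taking the genes as independent (Section 4.4), the chance of both claims is .830² = .689 under the fixed split. Under Holm both p-values must be ≤ .05 and at least one ≤ .025: .896² − (.896 − .830)² = .803 − .004 = .799.

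**The case against.** The strongest defence is that nothing here is an error. The responder proportion is the declared endpoint, repeated in Sections 1.1, 3.2.1, 4.4 and 13. Rates, test, level, size and power agree with one another, and the trial is adequately powered for the difference it calls important. An average shift also answers a different question from how many men respond. All of this stands, which is why the point concerns efficiency only.

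The second defence is that the gain is assumed. RNA yields are only 100-600 ng (Section 8.2), so outlying ratios are plausible, and with heavy tails a t-test or ordinary ANCOVA can do worse than Fisher. This also stands. It argues for a rank-based analysis, not for the yes/no cut.

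Four stronger readings are tempting, and the Protocol does not support them:

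- *An effect of realistic size would be missed.* No figure in the Protocol says what is realistic. The one pilot result (Section 2.4) is COX-2 decreased in four of seven men, 57%, close to the planned 60%, although it is not said to be a two-fold decrease.
- *Only a 40-point difference can be detected.* Power declines gradually: Fisher still has 71% at 35 points and 57% at 30.
- *The pairing of biopsies is lost.* Each response is a within-man change, so pairing is kept. Magnitude is what goes.
- *The .025 split is a mistake.* It is valid, and every power comparison in the two tables uses the same .025, so it is not the source of the loss.

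**Conclusion.** The sample-size statement is correct and the planned test is valid. The choice of primary analysis is inefficient, and the inefficiency is fixed in the Protocol itself. Under a normal log2 fold change, Fisher needs nearly twice the evaluable men (28 vs 15 per arm) for the planned effect, and gives up 15 points of power there and about 30 points at 20% vs 40-50%. These sizes rest on an assumed distribution. What does not rest on normality is that a rank test reached about 91-98% against Fisher's 83% at the planned rates in every distribution examined. The rank figures are for an unadjusted Mann-Whitney test. The extra gain from baseline was worked out only for the normal case and depends on an unknown correlation. The change is worth making but is not needed for validity.

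**What to change.** - **Primary analysis.** Prespecify a rank-based (robust) comparison of each supplement arm with placebo on 3-month log2 normalised expression, or on log2 fold change, adjusted for baseline log2 expression and the four diet strata. Name one outcome scale and one method in advance. Do not let an inspection of skewness decide: the symmetric heavy-tailed cases above would not trigger such a rule, yet they are where the t-test fails.
- **Supportive summary.** Keep the two-fold responder proportions by arm, with Fisher's exact test.
- **Sample size.** Leave 29 evaluable per arm and 97 accrued unchanged.
- **Optional.** Replace the fixed .025 split with Holm at the same overall one-sided .05. This is a minor free gain.

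**Cost.** No extra patients, biopsies or assays. The headline becomes an average shift rather than a responder rate. Sections 1.1, 3.2.1, 4.4 and 13 need amending, as does the restatement of the outcome in Section 2.1. The Protocol holds no SD, so the new sample-size text should keep the 20% vs 60% rationale and state the distribution assumed for the primary test.

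### Optional gain in efficiency: the primary Fisher's exact test is valid and meets its stated power, but Boschloo's test at the same one-sided .025 level would add about 2.5 to 6.5 points of power

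*Protocol*

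**What the plan says.** All the relevant statements stand in Protocol section 13, Statistical Considerations.

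- Test: "Fisher's exact test for proportions will be used" for comparing a supplement arm with placebo on *IGF-1* or *COX-2*. The outcome is binary for each man: at least a two-fold fall in transcript level, or not.
- Level: "The level of significance for a directional test is set at .025 because the control group will be compared with each of the two intervention" arms.
- Design point: "20% in control vs. 60% in intervention showing at least a two-fold decrease in mRNA level".
- Size: "29 patients will be randomized to the lycopene intervention, 29 to the fish oil intervention and 29 to the control arm". These are evaluable men; section 4.4 gives the same numbers.
- Power: "The power of each test is set at 81% (nQuery").
- Attrition: "The total accrual of 97 patients takes into consideration a 10% dropout rate by the time of the three-month biopsy".

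The section does not mention that Fisher's test is conservative, and it names no unconditional alternative. A Mantel-Haenszel test is held in reserve in case a stratified analysis is needed.

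**The concern.** Fisher's test conditions on the total number of responders. With 29 men per arm, only a few tables are possible for each total, so the attainable error rates are coarse and the test usually stops well short of its nominal level. Each comparison has a budget of .025, and any part of it that the test cannot spend is lost power.

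Boschloo's test ranks the tables by the same Fisher p-value. It sets the cut-off so that the error rate, maximised over every possible common response rate, stays at or below .025. It is therefore also exact, and its rejection region contains Fisher's. What is at stake is the chance of detecting a real effect with the tissue already planned, most of all for effects somewhat below the 40-point design difference, where power is lower.

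**Working it through.** **Inputs** (Protocol section 13): 29 evaluable men per arm; response rates 0.20 on placebo and 0.60 on supplement; one-sided .025 per comparison, which is how I read a directional test.

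**Formulas.** Let X be the number of responders on supplement, Y the number on placebo, and b(k; n, p) the binomial probability.

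- One-sided Fisher p-value: F(x, y) = Σ over k ≥ x of C(29, k)·C(29, x+y−k) / C(58, x+y).
- Power with cut-off c: Σ over tables with F(x, y) ≤ c of b(x; 29, 0.60)·b(y; 29, 0.20).
- True size with cut-off c: the maximum over p of Σ over the same tables of b(x; 29, p)·b(y; 29, p).
- Fisher's test uses c = .025. Boschloo's test uses the largest c whose true size is at most .025.

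All 30 × 30 tables were enumerated.

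**The plan's own figures.** Exact one-sided Fisher power is 80.2% at 27 per arm, 82.3% at 28 and 83.0% at 29. The continuity-corrected formula asks for 28 per arm for 81%. So 29 per arm delivers the stated 81% with about 2 points to spare. Accrual: 87 / (1 − 0.10) = 96.7, rounded up to 97, as stated.

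**Fisher v Boschloo at 29 v 29.**

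| | Cut-off on F | Maximum true size | Size at a common rate of 20% | Power, 20% v 60% |
|---|---|---|---|---|
| Fisher | .025 | 1.25% | 1.06% | 83.0% |
| Boschloo | .0410 | 2.40% | 2.19% | 89.0% |

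The gain is 88.96 − 83.01 = 5.9 points (5.95 before rounding).

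**What changes in practice.** With 6/29 responders on placebo and 14/29 on supplement, the Fisher p-value is .0259 (not significant) and the Boschloo p-value is .0146. With 5/29 and 12/29 they are .0410 and .0240. With 6/29 and 13/29 they are .0460 and .0271, so neither test rejects.

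**Other effects at 29 v 29.**

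| Placebo v supplement | Fisher | Boschloo |
|---|---|---|
| 10% v 50% | 90.0% | 94.1% |
| 30% v 70% | 81.4% | 87.9% |
| 20% v 55% | 71.3% | 79.6% |
| 20% v 50% | 57.2% | 67.1% |

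**Other final counts, 20% v 60%.** Both tests are discrete, so the gain moves with the exact numbers.

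| Supplement v placebo | Fisher size | Fisher power | Boschloo power | Gain (points) |
|---|---|---|---|---|
| 27 v 29 | 1.41% | 81.3% | 87.8% | 6.5 |
| 28 v 28 | 1.39% | 82.3% | 87.3% | 5.0 |
| 28 v 29 | 1.67% | 85.1% | 88.0% | 2.9 |
| 29 v 28 | 1.67% | 84.0% | 88.4% | 4.4 |
| 29 v 30 | 1.57% | 85.7% | 88.3% | 2.7 |
| 30 v 30 | 1.37% | 85.1% | 89.9% | 4.9 |
| 32 v 32 | 1.64% | 88.7% | 91.7% | 3.0 |
| 33 v 33 | 1.78% | 90.1% | 92.6% | 2.5 |

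In every row the Boschloo size stays at or below .025 and its rejection region contains Fisher's.

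**Equivalent in patients.** Fisher's test at 32 per arm has 88.7% power, level with Boschloo's 89.0% at 29. That is about 3 men per arm, or 3 × 3 = 9 across the trial.

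**The case against.** The strongest reply is that nothing in the plan is wrong. Fisher's test is valid, .025 is an upper limit that it respects, and the sample size already pays for its conservatism, since 83.0% exceeds the stated 81%. That stands in full. A reader might infer from a true size of 1.25% that the trial is underpowered or its error rate misstated; the protocol's own figures do not support that.

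The second reply is that 29 v 29 flatters the case, and this also stands. Among equal arms of 25 to 33, it is where Fisher's true size is smallest and the gain largest. The protocol accrues 97 men for 87 evaluable, randomises in blocks within four dietary strata (section 4.6), and censors men without a repeat biopsy by 14 weeks (note e to the study table). Exactly 29 v 29 is therefore unlikely, and half the error rate unused with 6 points gained is too strong as a general statement.

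Two further inferences should be resisted.

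- The case cannot rest on every man undergoing two research biopsy sessions. Tissue Bank donors may skip the baseline biopsy (section 8.2 and note b to the study table), and section 4.2 lets some men give research cores during a scheduled clinical biopsy.
- It might seem natural to extend the idea to a stratified mid-p test. Mid-p does not guarantee the level: unstratified, at nominal .025, its maximum size is 2.59% at 30 per arm and 2.79% at 31. It has no place in an argument that rests on exact control.

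**Conclusion.** The point holds as a gain in efficiency, optional in priority. At one-sided .025 and 20% v 60%, Boschloo's test adds 5.9 points at 29 v 29 and about 2.5 to 6.5 points across plausible final counts. It controls the level exactly and never loses a rejection that Fisher's test would make.

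This assumes the one-sided reading of the level, independent binomial counts, and an unstratified primary comparison. If .025 were meant as two-sided, the direction is the same: 75.4% for Fisher's test and 82.3% for Boschloo's at 29 v 29. The stated 81% fits the one-sided reading better. Only the protocol was available, so a separate analysis plan may already deal with this.

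**What to change.** In section 13, replace the Fisher sentence for the primary comparison with wording such as: *Each supplement arm will be compared with placebo by Boschloo's unconditional exact test, one-sided, at the stated .025 level; Fisher's exact test will be reported as a sensitivity analysis.* The sample size can stay as it is, and the 81% power statement remains true as a lower figure. The reserve Mantel-Haenszel analysis and the exploratory microarray tests need no change on this account.

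The cost is one sentence and standard software (SciPy has the test), with no added patients, biopsies or assays. The change must be made before unblinding, because results near the cut-off, such as 14/29 v 6/29, depend on which test is primary. If unblinding has already happened, Fisher's test should remain primary.
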